## Abstract

**Background:**

Hidradenitis suppurativa (HS) is a chronic, painful, inflammatory skin disease with estimates of prevalence in the European population of 1%–2%. Despite being a relatively common condition, the evidence base for management of HS is limited. European and North American management guidelines rely on consensus for many aspects of treatment and within the UK variations in management of HS have been identified. The HS James Lind Alliance Priority Setting Partnership (PSP) published a top 10 list of future HS research priorities including both medical and surgical interventions. The aims of the THESEUS study are to inform the design of future HS randomised controlled trials (RCTs) and to understand how HS treatments are currently used. THESEUS incorporates several HS PSP research priorities, including investigation of oral and surgical treatments. Core outcome domains have been established by the HIdradenitis SuppuraTiva cORe outcomes set International Collaboration (HISTORIC) and THESEUS is designed to validate instruments to measure the domains.

**Methods and analysis:**

The THESEUS study is a prospective observational cohort study. Participants, adults with active HS of any severity, will be asked to select one of five HS treatment options that is appropriate for their HS care. Participants will be allocated to their chosen treatment intervention and followed for a period of up to 12 months. Outcomes will be assessed at 3-monthly intervals using HISTORIC core outcome instruments. Video recordings of the surgical and laser operations will provide informational and training videos for future trials. Nested mixed-methods studies will characterise the interventions in clinical practice, understand facilitators and barriers to recruitment into future HS RCTs and examine patients’ and clinicians’ perspectives on HS treatment choices.

**Trial registration number:**

ISRCTN69985145.

Strengths and limitations of this studyIntroduces deroofing technique to the UK and re-tasks laser for hidradenitis suppurativa (HS) (rarely used for HS in UK before).Encourages multidisciplinary team working between dermatologists and surgeons and mirrors clinical practice with shared decision-making between patients and clinicians.Testing instruments developed by the HIdradenitis SuppuraTiva cORe outcomes set International Collaboration core outcomes set initiative.Limitation: Permitting treatment switches means efficacy data are more complex to analyse.Limitation: Delivery of conventional surgery was hampered by the COVID-19 pandemic.

## Introduction

### Background and rationale

Hidradenitis suppurativa (HS) is a chronic, inflammatory skin disease with global estimates of prevalence varying between 0.03% and 4% of the population; some of the variance is due to underdiagnosis.^1^ The clinical features of HS are recurrent, painful nodules and abscesses, often leading to skin tunnels and scarring. People with HS have significantly impaired quality of life due to both physical and psychological impact (eg, pain, suppuration of pus, social isolation and work disability).^2–4^

The evidence base for the management of HS is relatively sparse, as highlighted in a 2015 Cochrane review^5^ where only 12 randomised controlled trials (RCTs) with a total of 615 participants were identified. European and North American management guidelines rely on consensus for many of their recommendations as a result.^6–8^ Surveys of UK dermatologists have demonstrated variation in treatment strategies, suggesting there may be undesirable variance in treatment in the UK.^9^

The HS James Lind Alliance Priority Setting Partnership (PSP) published a top 10 list of future HS research priorities including both medical and surgical interventions.^10^ The THESEUS study incorporates several HS PSP priorities, including: what is the most effective and safe group of oral treatments in treating HS (ranked number one priority); what is the impact of HS and the treatments on people with HS (ranked third) and what is the best surgical procedure to perform in treating HS (ranked sixth). Across HS trials, there has been heterogeneity in outcome measurement. However, core outcome domains have now been established by the HIdradenitis SuppuraTiva cORe outcomes set International Collaboration (HISTORIC).^11^ THESEUS will contribute to the validation of HISTORIC outcome measurement instruments (OMIs), providing interpretation data and assessing feasibility.

### Objectives

#### Primary objectives

To inform the design of future HS RCTs and to understand how HS treatments are currently used.

#### Secondary objectives

To determine:

Feasibility of recruitment for future RCTs of HS treatments.Choice and characterisation of study interventions, (dose of medication, type of surgical techniques used).Current patient pathways and influences affecting patients’ and clinicians’ treatment choices.Choice, feasibility and responsiveness of OMIs, including evaluation of minimum important difference (MID).Consensus-agreed recommendations for future study designs.

Objectives of nested process evaluation studies and consensus workshop:

To characterise and document surgical and laser interventions.To understand patients’ perspectives on treatment choices and the implications of these choices for patients’ lives.To understand barriers to and facilitators for recruitment into future clinical studies of HS treatments.To identify up to three specific research questions suitable for future RCTs.To agree key elements of the design including participants and setting, intervention, comparator and outcomes.

An end of study consensus workshop aims to achieve consensus among key stakeholders over priority research questions and proposed study designs for future research into HS.

### Trial design

The THESEUS study is a non-randomised, prospective observational cohort study, with a nested process evaluation. Patient and public involvement (PPI) partners have been involved in the design and conduct of the study throughout.

## Methods: participants, interventions and outcomes

### Study setting

THESEUS will take place in up to 10 participating secondary care sites within the UK. Sites will be selected to reflect a breadth of specialty areas; these include those that offer a multidisciplinary team (MDT) approach, integrating HS medical and surgical care; those that have experience in HS surgery; and those with a dermatology department that is experienced in HS medical management. Participants will be identified from a search of local patient registers or from routine consultations.

THESEUS study funding commenced on 1 April 2019 and will finish on 30 September 2022.

### Eligibility criteria

Adults presenting to their hospital consultant with a diagnosis of active HS that is not adequately controlled by current treatment, and in whom at least one of the study interventions is appropriate for their care, will be approached to participate in the study.

Participants are eligible for the study if they meet all the following inclusion criteria and where none of the exclusion criteria apply:

#### Inclusion criteria

Adults at least 18 years old with active HS of any severity.Diagnosis meets disease definition: a lifetime history of at least five flexural skin boils or two flexural skin boils in last 6 months and confirmed by recruiting clinician with experience of HS care.HS is not adequately controlled by current treatment.At least one of the five study interventions is appropriate for the participant’s care.

#### Exclusion criteria

Unable or unwilling to give informed consent.Pregnancy or breast feeding.Not fluent in English, (questionnaires are only validated in English).

### Who will take informed consent?

Consent will be taken by suitably qualified Principle Investigators (PIs), coinvestigators and research nurses. The recruitment appointment will be carried out face–face for patients who are not known to the recruiter. However, for those patients who are already known to the study team, eligibility, consent and the baseline appointment can be performed remotely, if necessary, without the need for the patient to attend the hospital clinic. The option for remote recruitment was introduced via a protocol amendment as a result of the COVID-19 pandemic.

The consent form will have an option to approve being contacted about taking part in a study interview or joining an end-of-study consensus workshop. Prior to the interview, consent will be taken over the telephone by a study researcher; this process will be audio recorded. Participants who agree to attend the consensus workshop will not be asked formally for their consent, as their attendance will provide implied consent.

### PPI statement

Our PPI partners were involved as co-applicants on the THESEUS study grant and attend regular study management group meetings where they have input on study design (box 1).

Box 1Patient and public involvements (PPIs) contribution to the study designPPI and contribution to the study:Suggested to avoid chlorhexidine antiseptic washes as an intervention as this might perpetuate the concept of hidradenitis suppurativa being a condition of personal hygiene that contributes to further stigma.When discussing remote follow-up processes our PPIs highlighted it was key to offer participants options, that is, either video call or telephone with photographs of lesions provided or patient self-reporting their lesions as there would be different level of comfort felt by the participants.Suggested the addition of an ‘Opt Out’ message for the daily pain score text messages.PPIs suggested creating a specific deroofing video for patients (2600 views) as well as healthcare professionals (557 000 views) that avoids surgical jargon.Contributed to the planning of the consensus workshop, suggesting that at least one preworkshop meeting be held for patients in order to provide them with background information, including the aims of the workshop and how patients can contribute. Also, to offer the option of remote attendance for those unable to travel to the workshop.

### Interventions

#### Explanation for the choice of comparators

The choice of interventions that will be offered to patients in this study is informed by surveys completed by patients with HS (n=358), dermatologists (n=57) and plastic and general surgeons (n=225 responses analysed to date).^9^ We obtained PPI input through face–face discussion groups involving three people with HS and a partner of someone with HS. This PPI group recommended key changes to proposed study plans which have informed the current protocol (box 1). From these surveys and PPI feedback, five treatments were selected for the THESEUS study.

#### Intervention description

Our study design allows centres to offer standard care, where the clinician and patient feels this is most appropriate, as well as the opportunity to offer treatments that are less commonly used in the UK. Laser treatment and deroofing of skin tunnels are not standard treatments in the UK, but they are both included in the summary recommendations of the European HS guidelines.^12^ As the study is observational in design, normal National Health Service (NHS) waiting lists apply.

Participants can choose one of five treatment options, depending on their suitability as assessed by their clinician and on the availability of the options at each recruiting centre. Each site is required to provide at least four of the five interventions:

Oral doxycycline 200 mg one time per day for 6 months, with the option to continue for up to a further 6 months.Oral clindamycin and rifampicin both 300 mg two times per day as a combined course for 10 weeks, with the option to continue up to 6 months.Laser treatment using nd-YAG laser, (skin types 2–6) or alexandrite/diode laser, (skin types 1–3) administered on four occasions each 1 month apart.Deroofing of skin tunnels using electrocautery, (optimal protocol to be determined by UK experts and provided to centres as a training package including a video). It is expected that by following this training video, healthcare professionals including dermatologists and plastic surgeons will be able to perform the intervention. The procedure is carried out under local anaesthetic, repeated during the next 6 months if necessary. The total area treated at one time is limited by the volume of local anaesthetic needed and expected degree of impairment of activities of daily living during recovery. A training video was produced as part of the THESEUS study and so far has been viewed more than half a million times: https://www.youtube.com/watch?v=ftizgrBMzok.^13^Conventional surgery, (narrow or wide excision, with a range of closure methods depending on the preference of the clinician), with the option to receive another intervention or combination of interventions 6 months after the surgery and for up to a further 6 months.

Following the initial 6 months of the chosen intervention, participants have the choice to continue with the intervention or to switch to another intervention or combination of interventions.

### Criteria for discontinuing or modifying allocated interventions

Participants opting for an intervention with a substantial delay before receipt of the intervention, can choose to have another intervention during their wait time.

Participants are asked to stay on their chosen intervention for 6 months, after which they can either continue or switch to another intervention.

Participants who switch interventions during the first 6 months will be followed-up and the reason for the switch will be recorded.

### Relevant concomitant care permitted or prohibited during the trial

All concomitant care interventions are permitted at baseline because the study is observing usual care processes and the need for any additional concomitant care during the study will be documented.

### Provisions for post-trial care

Once a participant has completed the study period, they will revert back to regular NHS care. It is intended that centres offering deroofing may continue to provide this following the study, using the equipment provided by THESEUS and their experience of the procedure gained during the study.

### Outcomes

Primary outcomes measure(s):

Proportion of participants who are eligible, and hypothetically willing, to use the different treatment options at baseline.

Secondary outcomes measure(s):

Proportion of participants choosing each of the study interventions, with reasons for their choices.Proportion of participants who switch treatments within the first 6 months of treatment, with reasons for switch.Treatment fidelity over 6 months.Loss to follow-up rates over 12 months.Efficacy outcome estimates after 6 months of follow-up to contribute to OMI validation and to inform the end-of-study workshop regarding future RCT designs. Instruments include: lesion counts, HS Quality of Life Questionnaire (HiSQOL), Dermatology Life Quality Index (DLQI), Pain Numerical Rating Scale (NRS), Fatigue Questionnaire, Patient Global Assessment.

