##### Follow-up data collection

Follow-up reviews will be conducted over the telephone or at the outpatient clinic in person at 3 months, 6 months, 9 months and up to 12 months after the baseline appointment. The option for remote telephone follow-up was introduced via a protocol amendment, due to the COVID-19 pandemic and the subsequent restrictions on face-to-face appointments. Follow-up reviews are not anchored to treatment schedules and are conducted regardless of whether the participant has received their THESEUS intervention yet.

The clinical examination will be repeated at each follow-up review and recorded by the clinician. The measures completed at the baseline appointment, with the addition of a change in disease severity anchor measure, will be completed by the participant at each follow-up review.

The clinician will document which treatments or procedures the participant has received at each follow-up review using the intervention CRF. Clinicians will use this CRF to record intervention choice changes and any additions to the participant’s treatment regimen. An adverse event notification CRF is available at each review should the participant report any study-related adverse effects.

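### Switching is defined over six months of treatment but observed on a clock that starts at baseline, so late starters have an incomplete window that a crude proportion would hide

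*Protocol article*

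**What the plan says.** The Outcomes section defines one switching measure, the "Proportion of participants who switch treatments within the first 6 months of treatment, with reasons for switch". Its clock starts at treatment. The next item is "Treatment fidelity over 6 months", with no origin given.

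Observation runs on another clock. Follow-up data collection schedules reviews at "3 months, 6 months, 9 months and up to 12 months after the baseline appointment" and adds: "Follow-up reviews are not anchored to treatment schedules and are conducted regardless of whether the participant has received their THESEUS intervention yet". The Abstract likewise has participants "followed for a period of up to 12 months", so 12 months is a ceiling.

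Delayed starts are foreseen. Intervention description states that "normal National Health Service (NHS) waiting lists apply". The strengths and limitations list records that "Delivery of conventional surgery was hampered by the COVID-19 pandemic". The section on discontinuing or modifying interventions lets participants who face a substantial delay take another intervention while they wait.

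Two other sections use different time spans. The section on discontinuing or modifying interventions has reasons recorded for switches in the first 6 months, without saying from when. Statistical methods for primary and secondary outcomes describes adherence and switching over the whole study period.

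**The concern.** A proportion over a fixed window can be read directly only if each person in the denominator was observed for the whole window. Here, someone who starts treatment late in the follow-up year may be seen on treatment for only two or three months. Counted as a non-switcher, that person carries the same weight as one observed for all six.

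The loss need not fall evenly. Nothing in the article suggests a wait for the oral options, whereas surgery, and possibly laser and deroofing, depend on waiting lists. An option with long waits could then look more stable after start because it was watched for less time. Switching is one of the feasibility figures meant to inform future trials, so too low a figure would lead their designers to allow too little for crossover on that option.

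**Working it through.** **Inputs**

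- Outcome window: 6 months from treatment start (Outcomes).
- Follow-up F: at most 12 months from baseline (Follow-up data collection; Abstract).
- Delay s from baseline to treatment start: not given.
- True 6-month switch risk P: not given. Assumed 10%, 20% or 40%, with a constant hazard.
- Share f of a group that starts late: not given. Assumed 25% or 50%, all at month 9.
- Size of the least favoured option: the Sample size section expects 20 of 150. This reproduces: 150 × 0.13 = 19.5, rounded to 20.

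**Step 1: months of the window that can be observed.** W = max(0, min(6, F − s)).

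| Start month s | 0–6 | 7 | 8 | 9 | 10 | 11 | 12 |
|---|---|---|---|---|---|---|---|
| W if F = 12 | 6 | 5 | 4 | 3 | 2 | 1 | 0 |

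With full follow-up nothing is lost for any start up to month 6. With F = 9 the cut begins for starts after month 3. With F = 6 it begins with any delay.

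**Step 2: switch risk seen in one late starter.** Observed risk = 1 − (1 − P)^(W/6). For a start at month 9, W = 3 and the exponent is 0.5:

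- P = 10%: 1 − √0.90 = 5.1%
- P = 20%: 1 − √0.80 = 10.6%
- P = 40%: 1 − √0.60 = 22.5%

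**Step 3: crude group proportion, late starters kept in the denominator.** (1 − f)P + f[1 − (1 − P)^0.5].

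| True P | f = 25% | f = 50% |
|---|---|---|
| 10% | 8.8% | 7.6% |
| 20% | 17.6% | 15.3% |
| 40% | 35.6% | 31.3% |

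For P = 20% and f = 50%: 0.5 × 0.20 + 0.5 × 0.106 = 0.153. In a group of 20 that is about 3 switchers seen (20 × 0.153 = 3.06) against 4 expected (20 × 0.20).

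**Step 4: is the direction fixed?** Suppose half of the late starters take another treatment while waiting and this is counted as a switch. The crude figure becomes (1 − f)P + f[0.5 + 0.5(1 − (1 − P)^0.5)]. With f = 25% this gives 20.6%, 28.8% and 45.3% for true values of 10%, 20% and 40%, above the truth each time. The truncation lowers the figure for switching after start. The total reported figure can move either way.

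**The case against.** The strongest reply is that the article says only that a proportion will be reported. Denominators, censoring and incomplete windows are commonly left to the analysis plan, which is not shown, and the study is descriptive with no p values. That stands in part: the article does not fix a crude denominator, so it cannot be said to commit to a biased estimate. But the mismatch between the outcome's clock and the review schedule is in the article itself, and no analysis plan can recover observation after month 12.

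Four stronger readings are tempting and are not supported.

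- A reader might infer that switching is too low by construction for the procedures. That needs starts after month 6 (or shortened follow-up) and a crude denominator, and the article establishes neither. Hampered surgery could mean fewer operations rather than later ones, and step 4 shows that the net direction is open.
- A reader might infer that fidelity is cut in the same way. Its origin is not stated, so this follows only if it runs from treatment start.
- A reader might infer that the surgery arrangement, "with the option to receive another intervention or combination of interventions 6 months after the surgery and for up to a further 6 months", contradicts the 12-month limit. It is an option with an upper limit, not a required schedule, and follow-up also has an upper limit. With any wait, the later part of that option may go unobserved, but this is no contradiction.
- A reader might assume that exact switch dates are held. The article says that changes are recorded at each review, and the text-message section implies a known start day; it does not say that switch dates are recorded.

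**Conclusion.** The point holds in limited form. The outcome is defined from treatment start and observed from baseline, so any start after month 6 has an incomplete window, as does an earlier start if follow-up is shorter than 12 months. If those participants are kept as non-switchers, switching after start is understated for the options with long waits.

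The size cannot be derived from the article. It is zero if all start by month 6 with full follow-up. In the assumed cases above, a true 20% shows as 17.6% or 15.3% when a quarter or a half of the group start at month 9. These figures rest on assumed waits, an assumed risk and a constant hazard. The constant hazard may fit surgery poorly, since the option of another intervention opens 6 months after it. In a group of about 20 the loss is roughly one switcher, so this is a worthwhile, inexpensive improvement rather than a flaw that undermines the study.

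**What to change.** 1. Report 6-month switching for each option as a cumulative incidence from actual treatment start, with a 95% CI, censored at the last completed review. If exact switch dates are not held, use interval-level timing by review.
2. Give the number still under observation at 3 and 6 months on treatment. If nobody in an option is observed to 6 months, report only as far as the data reach.
3. Report treatment taken while waiting separately from switching after start.
4. State the origin of the 6-month fidelity window. If it is treatment start, restrict the measure to participants with 6 months observed after start.
5. Reconcile the time spans in Outcomes, the section on discontinuing or modifying interventions, Follow-up data collection, and Statistical methods, so that one origin and one window apply to each measure.

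No extra visits are needed if review-level timing is used. The price is wider intervals for the small procedural groups. Censoring also assumes that late starters switch at the same rate as early starters on the same option, and this should be stated with the result.
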